#### Trial design and overview

The WAVES study is a cluster-randomised controlled trial. Primary schools (n = 54) are recruited from a multi-ethnic population within the West Midlands, UK. Randomization is at the level of the cluster (school). Data are collected at both the cluster (school) and within cluster (individual pupils and their parents) level. To test the effect of the intervention, a range of anthropometric and psychological data are collected (described in detail later) on children within participating schools. Baseline measures are undertaken when the participating children are in Year 1 (April to July; aged 5 to 6 years). Schools are then randomly allocated to either the usual practice or intervention arm. Schools in the intervention arm are asked to implement a 12 month, multifaceted intervention programme (details below) when children are in Year 2 (aged 6 to 7 years). The programme includes physical activity and dietary components, targeting the school and family environments and aims to help children maintain a healthy weight, thereby preventing overweight/obesity. Due to practical considerations, half the schools (Group 1) are recruited to commence the study in the 2011/12 school year and the remainder (Group 2) in the 2012/13 school year. First follow-up measures are undertaken immediately after the intervention year (September to December, when the children are in Year 3; aged 7 to 8 years) and second follow-up measures are undertaken 18 months post intervention (January to March, when the children are in Year 4; aged 8 to 9 years). Group 1 schools receive a third set of follow-up measures 27 months post intervention completion (September to December when in Year 5; aged 9 to 10 years). A summary of the study design and timelines is shown in Figure 1.

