### Recruitment of study participants

All Year 1 pupils (aged 5 to 6 years) in participating schools were eligible to take part. An invitation letter, information leaflet and consent form were distributed through schools to parents/carers of eligible pupils.

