### Outcome measures

For clinical effectiveness, the primary outcome is the difference in body mass index (BMI) z-scores (using the UK 1990 BMI reference curves for children [26]) between arms at 3- and 18-month follow-up post-intervention completion. Secondary outcomes include: i) anthropometric measures: percentage overweight and obese (defined as a BMI greater than the 85th percentile on the UK 1990 reference charts for BMI centiles for boys and girls), skinfold thickness at 5 sites (biceps, triceps, thigh, suprailiac and subscapular), waist circumference and percentage body fat; ii) blood pressure; iii) dietary energy (kJ per kg body weight per day), fat, sugar, fibre (g/day), and fruit and vegetable intake (g/day and portions); iv) physical activity energy expenditure (kJ per kg body weight per day), and time spent doing sedentary, light, moderate and vigorous intensity activity (min/day), v) psychosocial outcomes to assess the wider effects of the intervention, including benefits and potential harms: health related quality of life and body dissatisfaction, and vi) longer term clinical effectiveness at 27 months post intervention in Group 1 schools.

For cost-effectiveness analysis, the primary outcome is cost per Quality-Adjusted Life Year (QALY). Other analyses will include cost per effectiveness outcomes such as change in BMI z-score and change in proportion of overweight/obese. A longer term model-based evaluation will predict cost-per-QALY outcomes over a lifetime by linking a change in weight status in childhood to future health outcomes in adulthood.

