### Data collection methods

Pupils’ date of birth, sex, ethnicity and postcode (to derive a proxy measure for deprivation) data are obtained from parent questionnaire, or if not available, from school records. Assessments are undertaken in school by trained research staff, using standardised procedures (available on request) and validated instruments at baseline and follow-up time points. In addition, parents of participating children are asked to complete questionnaires at each time point. These cover questions on child and parent demographics, dietary, sedentary, physical and sleep activity habits, home food environment, perceived neighbourhood environment and proximity to food and leisure facilities, family cooking habits and participation in leisure activities.

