### Planned statistical analysis

Trial analyses will be undertaken after the second follow-up measures are completed and there will be no interim analyses.

The baseline pupil (including sex, ethnicity, deprivation [based on IMD scores derived from home postcode] anthropometric measures, dietary intake, physical activity levels, psychological variables) and school level characteristics (school size, ethnic mix of pupils and % eligible for FSM) will be summarised by control and intervention arms, using numbers and proportions, means and standard deviations or medians and inter-quartile ranges.

Analyses of outcomes will be by intention to treat. As randomisation will be at the school (cluster) level, appropriate statistical methods to account for the clustering within schools (detailed below) will be used in the analysis. Analysis of outcomes will be for both 3- and 18-month follow-up stages.

We will use a mixed model ANCOVA with follow-up outcome values as the dependent variable and baseline values and treatment arm as the independent variables, to investigate effectiveness. These will be fitted using mixed models in STATA to allow for clustering. We will allow for clustering at the school level and explore the possibility of allowing for an additional level of clustering at the class level.

The primary analysis will be adjusted for baseline values for all outcomes. Secondary analysis will additionally adjust for pre-specified baseline school and child level covariates. These will include school level factors which were used in the randomisation (school size, % pupils eligible for free school meals, ethnic mix of pupils) and pupil level factors (sex, baseline BMI z-score, ethnicity, deprivation from home postcode, baseline total energy intake and baseline total physical activity). We will not adjust for age as all children will be of a very similar age. We will adjust at the school and pupil level for both ethnicity and deprivation as the school population is expected to differ from the consented study population.

Outcomes are either binary (e.g. non-overweight vs. overweight), or continuous (e.g. BMI z-score or energy expenditure), and therefore either log or linear link functions will be used, with transformations where appropriate to accommodate any non-normality. All model assumptions will be checked. We will report both relative and absolute treatment effects.

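### Ruling out age adjustment costs some precision in secondary outcomes not standardised for age, because the time from baseline to follow-up can differ between schools by 5 to 6 months

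*Protocol article*

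**What the plan says.** The protocol article (Planned statistical analysis) fits a mixed-model ANCOVA to each outcome, with its baseline value and treatment arm as predictors. A secondary analysis adds listed school and pupil covariates. Age is excluded explicitly, with a reason: "We will not adjust for age as all children will be of a very similar age".

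The design facts that bear on this are:

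- Recruitment of study participants: "All Year 1 pupils (aged 5 to 6 years) in participating schools were eligible to take part". This is a whole school year group.
- Trial design and overview, baseline: "Baseline measures are undertaken when the participating children are in Year 1 (April to July; aged 5 to 6 years".
- First follow-up: "September to December, when the children are in Year 3; aged 7 to 8 years".
- Second follow-up: "January to March, when the children are in Year 4; aged 8 to 9 years".
- Outcome measures: the primary outcome is BMI z-score "using the UK 1990 BMI reference curves for children", and overweight/obesity is defined on the same reference. Other secondary outcomes include "skinfold thickness at 5 sites (biceps, triceps, thigh, suprailiac and subscapular), waist circumference and percentage body fat; ii) blood pressure", with no age standardisation stated.
- Data collection methods: "date of birth, sex, ethnicity and postcode (to derive a proxy measure for deprivation) data are obtained", so age can be calculated.

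**The concern.** The sentence gives similar age as the reason for leaving age out of the models. Two children of the same age at entry can still be measured after quite different lengths of time. Waist, skinfolds, body fat and blood pressure can change as children grow, so a child followed for 20 months has had more time to change than one followed for 14.

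Measurement takes place in schools, so visit timing probably varies mainly from school to school. Schools are the randomised units. Variation at that level is not averaged down by measuring about 20 children in each school, and the baseline value carries no information about how long afterwards follow-up took place. At stake is avoidable between-school variance in the arm comparison for these secondary outcomes, which are already held to the 1% significance level.

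**Working it through.** The plan gives no figure for age spread or interval, so there is none to reproduce on this point. Its power statements do not depend on it.

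**Step 1. Intervals allowed by the windows, by named month**

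- First follow-up: shortest July to September of the following year, 14 months; longest April to December of the following year, 20 months. The difference is 6 months.
- Second follow-up: shortest July to January, 30 months; longest April to March, 35 months. The difference is 5 months.
- Counted from the first to the last day of each window, the limits are 13.1 to 21.0 months (a range of about 8) and 29.1 to 36.0 months (about 7).

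**Step 2. Spread of the interval between schools**

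The visit schedule is not given. Assume that visit dates are uniform over each window and independent between rounds. A uniform window of width w has variance w²/12.

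- First: 4²/12 + 4²/12 = 2.667, SD 1.63 months.
- Second: 4²/12 + 3²/12 = 2.083, SD 1.44 months.

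**Step 3. Effect on the arm contrast, using waist as the example**

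From the plan: 1000/50 = 20 children per school, and ICC 0.04 (the upper value given, for BMI z-score). Assumed, not in the plan: waist growth 1.5–2.5 cm/year, SD 6–7 cm, baseline correlation r 0.8–0.9, equal school sizes.

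- Variance of a school mean without timing noise: SD²(1 − r²) × [0.04 + 0.96/20] = SD²(1 − r²) × 0.088.
- Added variance: (growth/12)² × interval variance. This takes the slope on the baseline value as 1; a slope below 1 lowers it somewhat.

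*Least favourable to the point* (1.5 cm/year, SD 7, r 0.8): 49 × 0.36 × 0.088 = 1.552.
- First: (1.5/12)² × 2.667 = 0.0417, a rise of 2.7%; standard error +1.3%.
- Second: (1.5/12)² × 2.083 = 0.0326, a rise of 2.1%; standard error +1.0%.

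*Most favourable to the point* (2.5 cm/year, SD 6, r 0.9): 36 × 0.19 × 0.088 = 0.602.
- First: (2.5/12)² × 2.667 = 0.1157, a rise of 19.2%; standard error +9.2%.
- Second: (2.5/12)² × 2.083 = 0.0904, a rise of 15.0%; standard error +7.2%.

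**Step 4. Sensitivity to visit order**

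Let ρ be the correlation between a school's place in the baseline window and its place in the follow-up window. The interval variance is then 2.667(1 − ρ) at first follow-up and 2.083 − 2ρ√(1.333 × 0.75) = 2.083 − 2ρ at second.

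| ρ | First: variance rise | Second: variance rise |
|---|---|---|
| 0 | 2.7–19.2% | 2.1–15.0% |
| 0.5 | 1.3–9.6% | 1.1–7.8% |
| 1 (same order) | 0% | 0.1–0.6% |

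**Step 5. Cross-check without waist inputs**

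Let the outcome drift by g SD per year, and use the plan's variable school sizes (mean 25, SD 23), ICC 0.02–0.04 and the Step 2 timing at first follow-up. With r = 0.7, the standard error rises by 0.3–0.4% at g = 0.1, 1.1–1.6% at 0.2 and 2.5–3.5% at 0.3. With r = 0.9 and g = 0.3 it rises by 6.4–9.0%. The waist inputs correspond to g between 1.5/7 = 0.21 and 2.5/6 = 0.42.

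**The case against.** The strongest case for leaving the plan alone is that inference stays valid without the adjustment. A short prespecified covariate list is a defensible choice for secondary outcomes, and no conclusion is shown to change. The size also rests on a visit schedule that the article does not give and on waist inputs found nowhere in it. If schools are visited in the same order each round, the effect nearly vanishes. All of this stands, and it keeps the point minor.

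A reader might also draw three stronger conclusions that the article does not support.

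- *The 12-month age span of a year group adds between-school noise.* The span is real, and reaches about 16 months in age at measurement once the four-month baseline window is included. But the year-group part lies mainly within schools, and the baseline value absorbs much of it. Only visit timing acts at school level.
- *The arms are biased.* Under randomisation, chance differences in timing have zero expectation. Their standard error, 1.63 × √(2/25) = 0.46 months (0.06–0.10 cm of waist), is the variance of Step 3 seen from another side and must not be counted again. The school random effect carries it into the confidence interval. Nothing in the article shows scheduling by arm.
- *The primary result suffers.* BMI z-score is standardised for age, so it is essentially unaffected.

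Two further objections concern the remedy. The sentence does not name the interval, and visit timing is fixed after randomisation. Neither defeats the change. Age at follow-up given age at baseline is the interval, and ruling out age rules out both. Age at measurement is a standard covariate for growth-dependent outcomes. The post-randomisation timing is still a reason to report it by arm.

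**Conclusion.** The point holds as a minor precision improvement for waist, skinfolds, body fat and blood pressure. The stated reason for excluding age does not cover unequal elapsed time, which the plan's own windows allow to reach 6 months between schools at first follow-up and 5 at second. For waist, the variance of the arm contrast rises by about 3–19% at first follow-up and 2–15% at second.

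Those ranges are towards the upper end as regards visit timing, because they need independent, uniform visit dates. They also rest on the assumed growth rate, SD and correlation, and on an ICC borrowed from BMI z-score. Baseline age alone would not recover the loss; the model needs age at follow-up or the interval. The sample size and the primary BMI z-score analysis need no change.

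**What to change.** In the Planned statistical analysis section:

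- Restrict the no-age-adjustment sentence to outcomes already standardised for age (BMI z-score and overweight/obesity).
- For the other growth-dependent secondary outcomes (waist, skinfolds, body fat, blood pressure), prespecify age at baseline plus age at follow-up, or equivalently the baseline-to-follow-up interval, as covariates.
- Report the mean interval by arm at each follow-up.
- Leave the primary BMI z-score model as it is.

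The cost is a change of wording and two extra model terms. Date of birth is collected, and calculating a BMI z-score already requires age at each measurement. The drawback is small: one of the two terms, visit timing, is fixed after randomisation, which is why the interval should be shown by arm. The Trial status section puts the start of data analysis after June 2015, so at the time of the article the change could still be prespecified.

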### Justification of sample size

Sample size calculation is based on the primary outcome (BMI z-score). Further calculations were also performed to estimate power for the secondary outcome of percentage of children overweight or obese. Planned analysis of the WAVES study will compare outcomes for control and intervention schools at follow-up times, adjusting for baseline measurements. Therefore power calculations undertaken were based on repeated measures methods using estimates of correlation between before and after measurements. A modified version of the design effect [35] was used to estimate sample size and accommodate varying cluster sizes (using the estimated: mean cluster size (n = 25; SD = 23). For the primary outcome of BMI z-score, a follow-up sample size of 1000 children split across 50 schools gives the study greater than 90% power to detect a difference of 0.25 BMI z-score between intervention and comparator groups (equivalent to approximately 0.5 kg body weight for a 7-year old child) under all likely estimates of the intraclass correlation coefficient (ICC = 0 to 0.04, estimated correlation between before and after measures = 0.9 and estimated dropout rate = 20%). A change of 0.25 in BMI z-score has been shown to be associated with clinically detectable benefits in obese adolescents [36] and longitudinal studies demonstrate a linear relationship between BMI z-score in children as young as 7 and heart disease events in adulthood [4]. Under more conservative estimates for the ICC, this sample size would provide more than 80% power to detect a 0.125 difference in BMI z-score. A BMI z-score difference as low as 0.125 is the primary outcome of choice for other childhood obesity prevention trials [37]. Allowing for school drop-out (~8%), 54 schools were therefore invited to take part.

For the secondary outcome of percentage overweight/obese, this sample size (with an estimated correlation of before and after measures of 0.7 and an ICC of between 0 and 0.02) provides greater than 80% power to detect a difference in the change of proportion of children who are overweight/obese from baseline to follow-up in control compared to intervention schools of about 7% (exact value depends on baseline values). All power calculations were carried out in STATA using the clustersampsi function [38].

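### Read literally, the plan puts a log link on overweight/obesity in a secondary model that also contains baseline BMI z-score, and that combination gives fitted risks above 1

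*Protocol article*

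**What the plan says.** All of this is in the protocol article.

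- **Model** (Planned statistical analysis): a "mixed model ANCOVA with follow-up outcome values as the dependent variable and baseline values and treatment arm as the independent variables", with school clustering allowed for.
- **Link** (same section): "Outcomes are either binary (e.g. non-overweight vs. overweight), or continuous", and "therefore either log or linear link functions will be used". Taken in order, binary outcomes get a log link and continuous ones a linear (identity) link.
- **Covariates** (same section): the primary analysis adjusts each outcome for its own baseline value. For overweight/obesity that is most naturally binary baseline status. The secondary analysis adds school factors and "pupil level factors (sex, baseline BMI z-score, ethnicity, deprivation from home postcode", among others.
- **Effect measures** (same section): "We will report both relative and absolute treatment effects".
- **Outcome** (Outcome measures): overweight/obese is "defined as a BMI greater than the 85th percentile on the UK 1990 reference charts". It is one of several secondary outcomes. It has its own power statement in Justification of sample size, beginning "For the secondary outcome of percentage overweight/obese", and it also feeds a cost-effectiveness measure.

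**The concern.** Overweight at follow-up is a cut of the same quantity, BMI z-score, that enters the secondary model as a continuous covariate about two years earlier. With a before-after correlation of 0.9, a child well above the cut at baseline is almost certain to be above it at follow-up. True risk therefore climbs steeply and then levels off just below 1. A log link makes risk multiply by a constant factor for each unit of z-score, with no ceiling.

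A binomial likelihood does not allow fitted risks above 1, so the log-binomial model either breaks down or has no valid solution. If that happens at analysis, the link or the covariate set for this outcome would have to be changed with the data in view, unless a fallback is written elsewhere.

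**Working it through.** **Inputs from the article:** 1000 children in 50 schools at follow-up; before-after correlation of BMI z-score r = 0.9; ICC up to 0.04; cut at the 85th centile, i.e. z > 1.036.

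**Assumed, because the article does not give them:** z mean 0.2 to 0.5 and SD 1.1 to 1.2, so 22% to 33% overweight. At r = 0.9 the simulated correlation of overweight status was 0.69 to 0.71. The article assumes 0.7, so the scenario agrees with its own planning value.

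**Shape of the risk.** For bivariate normal z-scores with mean μ and standard deviation SD,

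risk(z₀) = Φ( [μ + r(z₀ − μ) − 1.036] / [SD·√(1 − r²)] ).

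With μ = 0.3 and SD = 1.15 the denominator is 1.15 × √0.19 = 0.501:

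| Baseline z | Risk at follow-up |
|---|---|
| 0 | 0.02 |
| 0.5 | 0.13 |
| 1.0 | 0.42 |
| 1.5 | 0.75 |
| 2.0 | 0.94 |
| 2.5 | 0.99 |

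From 0.5 to 1.0 the risk multiplies by 0.42/0.13 ≈ 3.2. The same factor once more gives 0.42 × 3.2 ≈ 1.3 at z = 1.5, where the true risk is 0.75. The gentler slope from 1.0 to 1.5 (0.75/0.42 ≈ 1.8) still gives 0.75 × 1.8 ≈ 1.35 at z = 2.0.

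**Simulated trials** (unequal schools, ICC 0.02 to 0.04, no treatment effect, r = 0.9, 200 replicates per scenario, log link):

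| Covariates besides arm | Proper log-binomial fit | Fitted risk |
|---|---|---|
| Binary baseline status (primary analysis) | 100% | highest about 0.79 to 0.83; never above 1 |
| Baseline z-score, with or without status (as in the secondary analysis) | 0% | Poisson fit above 1 in 100% of replicates; maximum about 3 to 6; about 3% to 6% of children |

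A separate run with z-score and arm gave risks above 1 in every replicate at r = 0.8 as well as at 0.9. Another, with both status and z-score (four scenarios of 300 replicates, z mean 0.3 to 0.5, SD 1.15 to 1.2), gave risks above 1 in every replicate, with a median maximum of about 3.

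**With a random school intercept** (160 fits). With binary baseline status, the fixed-part risk was below 1 in all 160 fits. With z-score it was below 1 in none; that result is only indicative, because the fitting routine capped risks at 1.

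**The alternative.** A logit link keeps every fitted risk below 1 by construction. With the same covariates, logistic regression followed by standardisation reduced the empirical SD of the log risk ratio by about 5% to 14% against the log link. The largest example was 0.076 against 0.088, and 1 − 0.076/0.088 ≈ 14%.

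**The case against.** **The wording is loose.** Linear is not the name of a link, so log may be shorthand for logit. If so, there is no fitting problem, but the text still needs correcting because the two links give different relative effects. As an illustration, take an assumed 26% falling by the article's 7 points to 19%. The risk ratio is 0.19/0.26 = 0.73, and the odds ratio is (0.19/0.81)/(0.26/0.74) = 0.67.

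**Detail may sit in an analysis plan that is not shown.** This is fair for the distribution, the estimation method and any fallback, and their absence from the article is no fault. But both the link and the z-score covariate are stated here, and they conflict as stated.

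**Fitted values above 1 need not spoil the treatment effect.** This stands in part. A marginal Poisson working model with school-robust standard errors is not excluded by the text. With z-score included, it gave arm risk ratios of 0.868, 0.750, 0.782 and 1.001 against simulated marginal values of 0.876, 0.744, 0.790 and 0.997. Uncorrected 95% coverage was 0.90 to 0.94. The likely damage is therefore a failed or impossible model and some lost precision, not a badly biased risk ratio.

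**The promise of relative and absolute effects is not itself an error.** The article does not say both must come from one fit.

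**A reader might infer that the primary model fails too.** It does not: with binary baseline status, every fit was proper. A reader might also reason that a normal school intercept on the log scale is unbounded, so some schools must have implied risks above 1. A school SD of 0.2 with a risk of 0.75 would indeed give P(Z > 0.288/0.2) ≈ 7.5%. But nothing in the article supports an SD of 0.2. The article takes an ICC of 0 to 0.02 for this outcome, and adjustment for baseline removes further school variation. The median fitted SD was 0 to 0.06, and the median chance of an implied school risk above 1 was at most 0.0002 (95th percentile 0.02 to 0.12).

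**Conclusion.** The point holds for models of overweight/obesity that contain continuous baseline BMI z-score. If log means log, the secondary, covariate-adjusted analysis has no valid log-binomial fit, or has fitted risks above 1, in essentially every simulated trial. This rests on the article's correlation of 0.9 and cut-off, on the assumed z means and SDs above, and on z-score entering as a linear term.

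The reach is limited. The primary-model analysis of this outcome and the continuous primary outcome are both unaffected. Nor does the article call overweight/obesity its main secondary outcome; it is one of many, though it has its own power statement and a place in the economic evaluation. This is a worthwhile, inexpensive correction and does not threaten the trial's main conclusion.

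**What to change.** In Planned statistical analysis, name the link for binary outcomes. At least in any model containing baseline BMI z-score, replace the log link with a logit link and keep the same covariates. Use either a logistic mixed model or a GEE with small-sample-corrected robust standard errors.

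Obtain the risk ratio and the risk difference by marginal standardisation. Predict each child's risk under both arms, averaging over the school effect if a mixed model is used. Average these risks over the trial sample and take their ratio and difference. Give 99% confidence intervals, in line with the article's 1% level for secondary outcomes, by the delta method or a school-level bootstrap. State also that the baseline value in the primary model for this outcome is binary status, if that is what is meant.

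The cost is a few words in the plan and one post-estimation step. Data collection and sample size do not change. The drawback is that the interval for the risk ratio no longer comes directly from a model coefficient.

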**Methods:**

This cluster randomised controlled trial is set in 54 primary schools within the West Midlands, UK, including a multi-ethnic, socioeconomically diverse population of children aged 6–7 years.

The 12-month intervention consists of healthy diet and physical activity promotion. These include: activities to increase time spent doing physical activity within the school day, participation in the ‘Villa Vitality’ programme (a programme that is delivered by an iconic sporting institution (Aston Villa Football Club), which provides interactive learning opportunities for physical activity and healthy eating), healthy cooking skills workshops in school time for parents and children, and provision of information to families signposting local leisure opportunities. The primary (clinical) outcome is the difference in body mass index (BMI) z-scores between arms at 3 and 18 months post-intervention completion. Cost per Quality Adjusted Life Year (QALY) will also be assessed. The sample size estimate (1000 children split across 50 schools at follow-up) is based on 90% power to detect differences in BMI z-score of 0.25 (estimated ICC ≤ 0.04), assuming a correlation between baseline and follow-up BMI z-score of 0.9. Treatment effects will be examined using mixed model ANCOVA. Primary analysis will adjust for baseline BMI z-score, and secondary analysis will adjust for pre-specified baseline school and child level covariates.

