The primary analysis will be a complete case analysis. However, missing data will be reported and associations between outcomes explored. Depending on the nature of these associations and the extent of the missing data, sensitivity analysis will be undertaken using multiple-imputation techniques.

The primary outcome and primary sub-group comparisons at both time points will be considered significant at the 5% level (and so 95% CIs reported); whereas other secondary outcomes will be deemed significant at the 1% level (and so 99% CIs reported). This difference in levels of significance, gives more weight to the primary outcomes.

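### The complete-case primary analysis ignores the 3-month value of children lost by 18 months, and the multiple-imputation check is conditional on what the data show

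*Protocol article*

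**What the plan says.** All of the following is in the protocol article.

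- **Analysis set.** Planned statistical analysis says "The primary analysis will be a complete case analysis". The same section says "Analyses of outcomes will be by intention to treat".
- **Missing data.** It adds that "sensitivity analysis will be undertaken using multiple-imputation techniques", but makes this depend on how missingness is associated with outcomes and how much there is. No criterion is given.
- **Primary model.** A mixed-model ANCOVA is fitted to the follow-up value, at the 3-month and 18-month stages. "The primary analysis will be adjusted for baseline values for all outcomes"; the abstract confirms this for the primary outcome: "Primary analysis will adjust for baseline BMI z-score, and secondary analysis will adjust for pre-specified baseline school and child level covariates".
- **Secondary model.** This adds the school factors used in randomisation and, at pupil level, sex, "baseline BMI z-score, ethnicity, deprivation from home postcode, baseline total energy intake and baseline total physical activity".
- **Expected loss.** Justification of sample size gives "estimated dropout rate = 20" percent, with 1000 children in 50 schools at follow-up.
- **Source of the added covariates.** Under Anthropometric measures, energy intake comes from a 24-hour tick list that parents complete for out-of-school hours. Activity comes from a monitor worn for 5 days. Both are measured at baseline, and Method of random allocation and blinding places randomisation after baseline.

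**The concern.** There are three linked issues.

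1. **The 18-month assumption.** A complete-case ANCOVA at 18 months is unbiased if, given baseline BMI z-score and arm, loss is unrelated to the 18-month outcome. A child seen at 3 months but not at 18 contributes nothing to the 18-month estimate, although the 3-month z-score is probably the best available predictor of the missing value. A model that uses it allows loss to depend on the 3-month value as well. Schools are told their allocation, so loss that differs by arm cannot be excluded.
2. **A conditional safeguard.** The only stated check on that assumption is run or not run after the data have been looked at, with no rule fixed in advance.
3. **Primary and adjusted estimates on different children.** If the secondary model is also fitted to complete cases, it drops any child without baseline energy intake or activity, even when both BMI values are present. A difference between the two estimates could then come from the adjustment or from the change of sample, and the reader could not tell which.

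**Working it through.** **Inputs from the article:** 50 schools, 1000 children at follow-up, mean cluster size 25 with SD 23, baseline to follow-up correlation 0.9, ICC 0 to 0.04, dropout 20%, differences of 0.25 and 0.125.

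**Assumed, because the article does not give them:** SD of BMI z-score 1; correlation between the two follow-ups (r12) 0.90 to 0.95; 25% to 100% of the children missing at 18 months seen at 3 months; all dropout taken at 18 months.

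**Step 1. Reproduce the plan's figures.**
- Children: 50 × 25 = 1250, and 1250 × 0.8 = 1000. So 250 are missing, and the 20% is already in the 1000.
- CV = 23/25 = 0.92. Follow-up mean cluster size is 1000/50 = 20.
- Design effect at ICC 0.04: 1 + ((0.92² + 1) × 20 − 1) × 0.04 = 2.437.
- Residual variance: 1 − 0.9² = 0.19.
- SE of the difference: √(4 × 0.19 × 2.437/1000) = 0.0430.
- Power at two-sided 5%: above 99.9% for 0.25 and 82.8% for 0.125. At ICC 0, power for 0.125 is 99.5%.

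The stated figures (above 90% and above 80%) hold.

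**Step 2. What a joint model adds at 18 months.** Given baseline, the two follow-ups correlate ρ = (r12 − 0.81)/0.19.
- r12 = 0.90: ρ = 0.474, ρ² = 0.224.
- r12 = 0.95: ρ = 0.737, ρ² = 0.543.

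With n_c = 1000 children seen at 18 months and n seen at either visit, the within-school variance factor changes from 1/n_c to (1 − ρ²)/n_c + ρ²/n. The between-school part, ICC × (1 + 0.92²)/50, is unchanged.

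Worked case: r12 = 0.95 and all 250 seen at 3 months (n = 1250).
- Within-school factor: 0.457/1000 + 0.543/1250 = 0.000891, against 0.001.
- ICC 0: √0.891 = 0.944, so the SE falls 5.6%.
- ICC 0.04: between-school part 0.001477. Total goes from 0.001477 + 0.96 × 0.001 = 0.002437 to 0.001477 + 0.96 × 0.000891 = 0.002333. The SE falls 2.2%.

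| r12 | Fall in SE, ICC 0 | Fall in SE, ICC 0.04 |
|---|---|---|
| 0.90 | 0.7% to 2.3% | 0.3% to 0.9% |
| 0.95 | 1.6% to 5.6% | 0.6% to 2.2% |

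The ranges run from 25% to 100% of the 250 seen at 3 months. Power for 0.25 stays above 99.9%. Power for 0.125 at ICC 0.04 rises from 82.8% to at most 84.3%.

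**Step 3. Possible bias (illustration only).** If the 20% missing in one arm differ from those observed by d, given baseline, and there is no such difference in the other arm, the bias is 0.2 × d.
- d = 0.10 gives 0.02.
- d = 0.25 gives 0.05, which is 0.05/0.125 = 40% of the smaller difference the article claims power for. This d is large: the residual SD is √0.19 = 0.44.

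Nothing in the article says how large d is.

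**Step 4. The adjusted model.** Assume that 10% to 30% lack activity data and 10% to 30% lack diet data, independently. Retention is then between 0.7 × 0.7 = 49% and 0.9 × 0.9 = 81%.
- ICC 0: 1/√0.81 = 1.11 and 1/√0.49 = 1.43, so the CI is 11% to 43% wider.
- ICC 0.04, 81% kept: cluster size 16.2, design effect 2.156. √((2.156/0.81)/2.437) = 1.045.
- ICC 0.04, 49% kept: cluster size 9.8, design effect 1.684. √((1.684/0.49)/2.437) = 1.187.

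So at the ICC of 0.04 the widening is about 4% to 19%.

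**The case against.** An ANCOVA at each visit on observed outcomes is a standard choice, and it is valid when missingness depends only on baseline and arm. The article promises to report missing data and foresees imputation, and the planned 1000 already allows for the 20% loss. All of that stands. Several stronger readings are tempting, and the article does not support them.

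- **That a missing diet or activity value removes a child from the primary analysis.** It does not. The primary BMI z-score model adjusts for baseline BMI z-score only; "baseline total energy intake and baseline total physical activity" belong to the secondary model.
- **That a child with one follow-up is discarded.** Nothing requires both values. The child counts at the visit where measured. Even if both were required and 800 children remained, power for 0.25 would stay above 99.9%, and power for 0.125 at ICC 0.04 would be 79.1%.
- **That the analysis is not intention to treat.** Nothing suggests that children are analysed other than as randomised. The gap is an incomplete set under an unstated assumption. A joint model also leaves out children with no follow-up.
- **That precision is badly hurt.** The 22% to 54% recovery (ρ² above) is per child missing at 18 months, not for the trial.

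It is also fair to say that the article ties complete-case handling to the primary analysis and is silent on missing covariates in the secondary model. A fuller plan may settle that, so this part of the point is conditional.

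The objection does not remove the rest. The article itself fixes the primary estimator and itself makes the only stated missing-data check depend on the data.

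**Conclusion.** The point holds as a matter of validity and pre-specification, not of power. With 20% loss expected, the 18-month result rests on an unstated assumption stronger than it needs to be, and the check on it is not guaranteed to be run. The precision at stake is small: at most about 2% of the 18-month standard error at ICC 0.04 and under 6% at ICC 0. The possible bias cannot be sized from the article. For the adjusted model, if complete-case handling applies, the main harm is loss of comparability with the primary estimate. The CI widening of about 4% to 19% at ICC 0.04 (11% to 43% only at ICC 0) depends wholly on the assumed missingness of diet and activity data. All figures also assume an SD of 1, and the joint-model figures assume the follow-up correlations and dropout pattern given above. This is a worthwhile, cheap improvement; the primary analysis as planned is not invalid.

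**What to change.** 1. Fit one linear mixed model to both follow-ups, with arm by visit, baseline by visit, and school and child random effects, using every child with a baseline value and at least one follow-up. Report the arm difference at each visit from it. If the ANCOVA at each visit is kept as primary, at minimum run the multilevel multiple-imputation sensitivity analysis unconditionally and include the 3-month value in the imputation model.
2. In the secondary adjusted model, fill missing pre-randomisation covariates by mean imputation or a missing indicator, so that no child with an outcome is dropped and both estimates rest on the same children.
3. Beside the intention-to-treat statement, say which children are included and what is assumed about those who are missing.

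The cost is a little more analysis work and a few sentences of text. No new data are needed.
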